### Trial design

The trial is a two-arm parallel group multicentre pragmatic superiority randomized controlled trial (RCT), with a 1:1 allocation at the individual level. The group SMS intervention will be offered to participants in the TAU groups after the 12-month follow-up (delayed-intervention). The 24-month follow-up will therefore only provide a within-group dataset. The proposed protocol conforms to SPIRIT guidance [40].

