## Methods

### Participants, interventions, and outcomes

#### Study setting

The study will be conducted in four health administrative regions in Quebec (Canada): Eastern townships, Mauricie-et-Centre-du-Québec, Abitibi-Témiscamingue and Laurentides. Administrative regions were purposefully selected based on the following criteria: a) the in-person group SMS intervention is not currently largely implemented in the region; b) the virtual SMS intervention is rarely accessed by participants from the region, even though the virtual SMS format is technically accessible throughout the province; c) diversity (e.g., population size, region, university teaching hospital).

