#### Assignment of interventions: Sequence generation, allocation concealment mechanism and implementation

Participants will be randomized based on stratification for study site, with random block sizes (2, 4, 6) to ensure a balance in the allocation for the strata. The randomization schema will be carried out using a code generated by the study statistician. Concealment will be maintained for the participants, research team, and staff. The REDCap computerized platform will only release the randomization code to the research coordinator based on the allocation sequence after verification of eligibility. The research coordinator will then enrol and assign participants to interventions.

The randomization sequence will be recorded with random codes (“A” and “B”) until the primary outcome analyses are concluded. Masking of trial participants and facilitators is not possible in this trial. Clinical evaluations at T_3_ and T_4_ will not be masked as we will address through qualitative interviews patient experience following the SMS intervention, or readiness to enroll intervention at T_3_ for the control group.

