#### Statistical Analyses

##### Clinical outcomes

Statistical analysis will follow intent-to-treat principles. The primary outcome analysis will be performed at T_1_. The remaining analysis will be conducted considering all measures over time when all participants have completed the 12-month (T_0_ through T_3_) and 24-month follow up (T_0_ through T_4_). Primary question: A mixed model regression with the maximum-likelihood method will be performed to consider between- and within-subject variations in the analysis of the longitudinal effects of SMS + TAU compared to TAU on the primary outcome measure (BAI) at post-treatment (T_1_). To control for potential intra-group variability, random effects will be added on the participants nested in the SMS groups. Baseline clinical variables (e.g., anxiety disorders, comorbid depressive symptoms, psychotropic medication, psychotherapy) will be entered in the model as covariates. Analyses will be conducted with all available data without imputation, as estimation of parameters by maximum likelihood is considered adequate to address missing data as post-treatment in the multilevel model [74, 75].

For secondary questions, logistic regression models will be used to examine high-end functioning rates. The mixed model regression approach will be repeated on all data at the 12-month (T_0_ through T_3_) and 24-month (T_0_ through T_4_) follow-up, and will allow for the inclusion of patients with missing data at any of the follow-up assessments (T_1_,T_2_,T_3_,T_4_). Additionally, treatment effect sizes will be estimated with Cohen’s *d*. We will also conduct hypothesis-generating moderator and mediator analysis [76]. Moderation analyses will be performed for three sets of moderators, including clinical characteristics (e.g., anxiety disorders at baseline, anxiety severity, comorbid depression), previous treatments (psychotropic medication, psychotherapy) and sociodemographic characteristics (e.g., age group, sex, education level). Mediators will be examined for therapeutic alliance, group cohesion and adherence. Sensitivity analysis will be applied to examine the influence of missing data, and to document *per protocol* treatment effects (≥ 8 sessions completed).

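### Randomisation is stratified by study site, but the described primary model has no site term, so the standard error may be slightly too large

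*Protocol article*

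**What the plan says.** The section on assignment of interventions makes study site the only stratification factor: "Participants will be randomized based on stratification for study site, with random block sizes (2, 4, 6"). The stated purpose is balanced arms within each stratum. Allocation is "with a 1:1 allocation at the individual level" (Trial design). On where the trial runs, Study setting says: "The study will be conducted in four health administrative regions in Quebec (Canada"). One of its three criteria for choosing the regions is "diversity (e.g., population size, region, university teaching hospital").

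The primary model is set out under Statistical Analyses, Clinical outcomes: "A mixed model regression with the maximum-likelihood method will be performed to consider between- and within-subject variations". On clustering, "random effects will be added on the participants nested in the SMS groups". On adjustment, "Baseline clinical variables (e.g., anxiety disorders, comorbid depressive symptoms, psychotropic medication, psychotherapy) will be entered in the model as covariates". The same approach is then repeated on the 12-month and 24-month data. Site is not named as a fixed effect, random effect, covariate or moderator in that section.

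**The concern.** Blocking within site makes the arms nearly equal in every site, so differences between sites contribute almost nothing to the sampling error of the arm comparison. A model without a site term does not know this. It keeps the between-site variance in the residual and reports a standard error that is too large for the design used.

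The result would be confidence intervals a little too wide, a test run a little below its nominal level, and the loss of some of the precision that stratification provides. Sample size already puts power at about 76% once correlation within SMS groups is counted, so a free gain is worth taking.

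The SMS-group random effect does not stand in for site. Groups exist in one arm only, they meet online, and the article does not say that they are formed within region.

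**Working it through.** **Inputs from the article (Sample size, unless noted).** Difference 4 points, pooled SD 12.5, 80% power, α = 0.05, 155 per arm, 25% attrition, 207 per arm, ICC 0.02; SMS group size 10–15 (Interventions).

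**Reproducing the plan's figures.** d = 4/12.5 = 0.32. A two-sided two-sample t-test (noncentral t) needs 155 per arm, with power 80.2%. 155/0.75 = 206.7, rounded up to 207. With a design effect of 1 + (m − 1) × 0.02 in the SMS arm only, power is 77.0%, 76.0% and 75.1% for m = 10, 12.5 and 15, which agrees with the stated figure at the middle group size. None of this depends on site.

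**Assumed input.** Let ρ be the between-site share of variance in the quantity analysed: T1 BAI given the covariates, or T0–T1 change if T0 is in the outcome vector. The article does not give ρ, so a range of 1% to 10% is used.

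**Formulas (155 per arm, before the group ICC).**
- Reported SE without site = 12.5 × √(2/155) = 1.420.
- True SE, which is also the SE with site in the model = 1.420 × √(1 − ρ).
- Overstatement = 1/√(1 − ρ) − 1.
- Actual type I error without site = 2 × [1 − Φ(1.96/√(1 − ρ))].
- Power without site = Φ[(4 − 1.96 × 1.420)/true SE].
- Power with site = Φ(4/true SE − 1.96).

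| ρ (assumed) | True SE | SE overstated by | Type I error without site | Power without site | Power with site |
|---|---|---|---|---|---|
| 1% | 1.413 | 0.5% | 0.049 | 80.5% | 80.8% |
| 2% | 1.406 | 1.0% | 0.048 | 80.7% | 81.2% |
| 5% | 1.384 | 2.6% | 0.044 | 81.0% | 82.4% |
| 10% | 1.347 | 5.4% | 0.039 | 81.7% | 84.4% |

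For ρ = 5%, power without site is Φ[(4 − 2.783)/1.384] = Φ(0.879) = 81.0%, and with site it is Φ(2.890 − 1.96) = Φ(0.930) = 82.4%.

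**Simulation check.** 6000 runs, blocks of 2, 4 and 6 within four sites, 310 completers. Site sizes (120, 80, 60, 50) and a T0–T1 correlation of 0.5 before site effects are assumptions.
- Site effects on both level and change, 5% each, change analysis: without site, mean reported SE 1.420 against an empirical SD of 1.382, type I error 0.043. With site, 1.384 against 1.382, type I error 0.048.
- Site effect on level only, 5%, change analysis without site: mean reported SE 1.383 against an empirical SD of 1.375, type I error 0.051. Omitting site does nothing here, because a stable level difference cancels in the change score.
- Site effect on level only, 5%, T1 score adjusted for T0, without site: mean reported SE 1.209 against 1.198, type I error 0.047. Most of the site effect is already absorbed by T0.

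**The case against.** The strongest reply is that the article never excludes site. It condenses the model into a few sentences and gives the covariates as examples, and an analysis plan not shown may include the stratification factor. In part this stands: the text shows that site is unnamed, not that it was rejected. But the examples only leave open which clinical variables enter, and site is not a clinical variable. An analyst who followed the section as written would fit a model without it.

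The second reply is that the effect depends on the form of the model, and this stands in full. The section speaks of longitudinal effects and the sample size rests on the pre-post difference. In an arm-by-time contrast only site differences in change matter, so the share of T1 variance is then the wrong quantity. Covariates already in the model may also absorb some of the site variance.

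A reader might infer that the regions were chosen to differ in outcome. The article does not support that. Diversity is one of three selection criteria and concerns population size, region and teaching hospital. The other two select regions that are alike in low uptake of the programme. Delivery is virtual and the outcomes are online self-reports. Usual care is unrestricted and could vary by region, but nothing in the article points to a share as high as 5% or 10%.

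The cost models should not be counted as part of the mismatch. Economic evaluation outcomes already allows adjustment for confounding study factors in wording open enough to include site.

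**Conclusion.** The mismatch is in the text: the only stratification factor is missing from the model as described. Its consequence is small, conservative and conditional. For an assumed site share of 1% to 10% in the analysed quantity, the standard error is overstated by about 0.5% to 5.4%, type I error is 0.049 to 0.039, and the power loss is about 0.3 to 2.7 percentage points. The lower end applies if sites differ little. The effect is zero if sites differ only in stable level and the contrast is arm-by-time.

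A reader might go further and conclude that the primary result would be biased, that false positives would rise, or that the trial is undersized because of site. None of these follows. The estimate stays unbiased, the error is on the conservative side, and the stated sample size reproduces without any site term. The 76% power figure reflects correlation within SMS groups, not site.

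**What to change.** State site as a fixed effect in the primary BAI mixed model and in its between-arm repeats through T3. If T0 is modelled as an outcome, add site-by-time terms as well, because a site main effect alone does not touch the arm-by-time contrast. The 24-month data are within-group only according to Trial design, so they are not part of this.

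Reading site as the four regions, the cost is 3 degrees of freedom for the main effect plus 3 for each added time point: 6 for T0 and T1, 12 for T0 through T3, against about 310 completers. If the strata are finer than the regions, the cost rises and the number of levels should be stated. If site is also added to the logistic model for high-end functioning, say that the odds ratio is then conditional on site. The 155 and 207 per arm do not change. Fixing the term before the allocation codes are opened also removes a later choice about whether to include site.

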#### Sample size

Due to challenges in calculations for mixed regression models [68], we estimated sample size based on the baseline (T_0_) and post-treatment (T_1_) difference between groups for the primary outcome. The sample size was calculated using G*Power with the BAI based on an estimated effect size of the SMS + TAU intervention (Cohen’s *d*) of 0.32 (0.56 intra-group). This corresponds to a 7-point difference based on previous studies [51] that have established *clinically significant change* thresholds for the BAI [69]; such an effect size at post-treatment for symptom reduction is consistent with previous SMS studies for mental disorders [25, 35, 37, 38] as well as with pilot data of SMS (conservative estimates). The 3-point difference and SD for the TAU only group are conservative values based on our current data in a similar study with a TAU group [70]. A sample size of 155 individuals per group is therefore required to detect a 4-point (pooled SD: 12.5) pre-post treatment difference between SMS + TAU and TAU (i.e., a 7-point difference for SMS + TAU and 3-point for TAU) with an 80% power and α = 0.05. As there is a potential for intraclass correlations (ICC) in an individually randomized group treatment trial [71], we also estimated [72, 73] that based on a mixed model accounting for possible between-individual correlations within each intervention group (ICC of 0.02 for based on a similar study [70]), the power would be of at least 76%. With an adjustment for a conservative 25% attrition rate, the proposed sample size is 207 individuals for each treatment arm.

#### Statistical Analyses

##### Clinical outcomes

Statistical analysis will follow intent-to-treat principles. The primary outcome analysis will be performed at T_1_. The remaining analysis will be conducted considering all measures over time when all participants have completed the 12-month (T_0_ through T_3_) and 24-month follow up (T_0_ through T_4_). Primary question: A mixed model regression with the maximum-likelihood method will be performed to consider between- and within-subject variations in the analysis of the longitudinal effects of SMS + TAU compared to TAU on the primary outcome measure (BAI) at post-treatment (T_1_). To control for potential intra-group variability, random effects will be added on the participants nested in the SMS groups. Baseline clinical variables (e.g., anxiety disorders, comorbid depressive symptoms, psychotropic medication, psychotherapy) will be entered in the model as covariates. Analyses will be conducted with all available data without imputation, as estimation of parameters by maximum likelihood is considered adequate to address missing data as post-treatment in the multilevel model [74, 75].

For secondary questions, logistic regression models will be used to examine high-end functioning rates. The mixed model regression approach will be repeated on all data at the 12-month (T_0_ through T_3_) and 24-month (T_0_ through T_4_) follow-up, and will allow for the inclusion of patients with missing data at any of the follow-up assessments (T_1_,T_2_,T_3_,T_4_). Additionally, treatment effect sizes will be estimated with Cohen’s *d*. We will also conduct hypothesis-generating moderator and mediator analysis [76]. Moderation analyses will be performed for three sets of moderators, including clinical characteristics (e.g., anxiety disorders at baseline, anxiety severity, comorbid depression), previous treatments (psychotropic medication, psychotherapy) and sociodemographic characteristics (e.g., age group, sex, education level). Mediators will be examined for therapeutic alliance, group cohesion and adherence. Sensitivity analysis will be applied to examine the influence of missing data, and to document *per protocol* treatment effects (≥ 8 sessions completed).

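### The SMS-group random effect is not tied to post-baseline BAI; fitted as the usual constant nested intercept, it would leave the clustering allowed for in the power out of the primary standard error

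*Protocol article*

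**What the plan says.** The Sample size section of the protocol article powers a difference in change: "we estimated sample size based on the baseline (T_0_) and post-treatment (T_1_) difference between groups for the primary outcome". The target is to "detect a 4-point (pooled SD: 12.5) pre-post treatment difference between SMS + TAU and TAU", "with an 80% power and α = 0.05", which gives 155 per arm. The section recognises that individually randomized patients treated in groups may be correlated. It therefore re-evaluates power under a mixed model "accounting for possible between-individual correlations within each intervention group", with an ICC of 0.02, and reports at least 76%.

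The Clinical outcomes section then sets out the primary analysis: "A mixed model regression with the maximum-likelihood method will be performed to consider between- and within-subject variations" for BAI at T1. Clustering is handled in one sentence. To control variability within groups, "random effects will be added on the participants nested in the SMS groups". The article does not say whether the group effect is constant over time or acts only after baseline.

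The Recruitment section places randomization after the T0 questionnaires are complete, and Table 2 (study schedule) places the baseline BAI at T0.

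**The concern.** Correlation from shared sessions and facilitators can arise only once sessions begin. It is present at T1 and absent at T0. A group effect does its job in this design only if it acts on the post-baseline score.

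The sentence in the plan names a hierarchy (participant within SMS group) and no time component. Most analysts would code that as two nested random intercepts. A group intercept shared by T0 and T1 drops out of every participant's change, and so out of the arm-by-time estimate. The analyst would follow the text, believe that clustering had been handled, and report nearly the standard error obtained by ignoring the groups.

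At stake are a primary confidence interval that is somewhat too narrow, and a mismatch between the sample size section, which allows for this variance, and the analysis section, which may omit it.

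**Working it through.** **Is T0 an outcome row?** The article does not say so outright for the primary model, but four points favour it. Within-subject variation cannot be estimated from one row per person. The powered quantity is the T0-to-T1 change. The same approach is later repeated on T0 through T3. The examples of baseline covariates do not include baseline BAI.

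**Inputs from the documents.** Difference 4; SD 12.5; alpha 0.05 (taken as two-sided, which reproduces the sample size); 155 per arm before attrition and 207 after; ICC 0.02; SMS groups of 10 to 15.

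**The plan's own figures.**
- Effect size 4/12.5 = 0.32. The noncentral t gives 80.2% power at 155 per arm, and 155/0.75 = 207. Both reproduce.
- Power with clustering in the SMS arm only: DE = 1 + (m − 1) × 0.02 and SE = 12.5 × √((DE + 1)/155). For m = 10, DE = 1.18, SE = 1.482 and power is 77.0%. For m = 12, DE = 1.22, SE = 1.496 and power is 76.2%. For m = 15, DE = 1.28, SE = 1.516 and power is 75.1%. The stated 76% is therefore what results when the clustering is in the SE of the contrast.

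**Why a constant intercept cancels.** Let participant i in group j at time t have Y = fixed part + g_j + u_i + e_it. The change from T0 to T1 is the fixed change + e_i1 − e_i0, without g_j. The model's variance for the difference in change between arms is 2σe²(1/n1 + 1/n0). In truth the group effect enters at T1 only, which adds σg²/J for J groups.

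**Number of groups.** 207/15 ≈ 14 and 207/10 ≈ 21 groups are formed. With 155 analysed, that is about 11.1 or 7.4 per group.

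**Case A: 12.5 is the SD of change.** Variance of change V = 156.25; σg² = 0.02 × 156.25 = 3.125. The single residual variance is pooled over the arms, so 2σe² = 156.25 + 3.125/2 = 157.81.
- Model variance: 157.81 × 2/155 = 2.036, SE 1.427.
- True variance, J = 14: 156.25 × 2/155 + 3.125/14 = 2.016 + 0.223 = 2.239, SE 1.496. Ratio 0.954; type I error 2Φ(−1.96 × 0.954) = 6.2%.
- True variance, J = 21: 2.016 + 0.149 = 2.165, SE 1.471. Ratio 0.970; type I error 5.7%.

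**Case B: 12.5 is the score SD and the T0-T1 correlation is 0.7 (assumed).** V = 2 × 156.25 × 0.3 = 93.75. With a correlation of 0.5 instead, V = 156.25 and Case A applies.
- Model variance: (93.75 + 1.5625) × 2/155 = 1.230, SE 1.109.
- J = 14: 1.210 + 0.223 = 1.433, SE 1.197. Ratio 0.926; type I error 6.9%.
- J = 21: 1.210 + 0.149 = 1.358, SE 1.166. Ratio 0.951; type I error 6.2%.

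**Fewer groups.** With only 10 groups of 15 analysed, the ratio is 0.936 (type I error 6.7%) in Case A and 0.900 (7.8%) in Case B.

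**Does another treatment of baseline help?** Constraining the arms to equal means at T0, with the intercept still constant over time, gives 6.0 to 8.2% across groups of 8 to 15 analysed and both cases. It is not a cure.

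**Maximum likelihood with few groups.** In simulation with the group effect correctly placed at T1, ML with a z-test gave 5.3 to 5.6% at ICC 0.02. REML with Satterthwaite degrees of freedom gave 4.6 to 5.3% (ICC 0.02 and 0.05).

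**The case against.** The strongest reply is that the failing model is not in the text. The article says random effects, in the plural, and never says intercept. A group-by-time effect fits those words and carries the clustering. The sentence states its purpose, which is to control variability within groups, and the 76% power agrees with a model that does so. The primary analysis is described as performed at T1; if baseline BAI is a covariate and T1 the only outcome, the problem disappears. A full analysis plan, not shown, may settle the form.

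Much of this stands. A reader might infer that the primary standard error is definitely wrong. The article does not support that, because it leaves open a form that works. A reader might also expect a badly inflated type I error. That would need an ICC larger than the documented 0.02, and the documents give no such value. Nor is it a finding that "logistic regression models will be used to examine high-end functioning rates" appears without a group term: that is a short sentence on a secondary question, of a kind often completed elsewhere.

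The reply does not remove the ambiguity. The article chose to specify the clustering term for its primary endpoint, and the most ordinary implementation of that specification does not serve its stated purpose.

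**Conclusion.** The concern holds in conditional form. If the SMS-group term is fitted as a time-constant intercept in a model with T0 and T1 as outcomes, the clustering budgeted in the sample size section does not reach the standard error of the contrast that section powers. At the plan's own ICC of 0.02, the standard error is then about 3 to 5% too small and the type I error about 5.7 to 6.2%. It is about 6.2 to 7% under the assumed correlation of 0.7 with 12.5 as score SD, and up to about 8% with only 10 groups.

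These figures assume a group effect at T1 only, equal group sizes, 155 analysed per arm and a large-sample normal reference. The use of ML is a minor point at this ICC. The distortion is small but avoidable, and it is best settled before the data are analysed.

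**What to change.** In the Clinical outcomes section, state that the SMS-group random effect acts on post-baseline BAI only and in the SMS arm only, with each TAU participant treated as a singleton. An equivalent route is to model T1 BAI with baseline BAI as a covariate and an SMS-group random effect. In either case, fit by REML with Satterthwaite or Kenward-Roger degrees of freedom, because there are few groups.

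This takes about two sentences and brings the analysis into line with the power statement. The price is a slightly wider confidence interval: in Case A the SE rises from 1.427 to between 1.471 and 1.496. That corresponds to power of about 76 to 78% (4/1.496 − 1.96 = 0.71 and 4/1.471 − 1.96 = 0.76 on the normal scale), which the plan already accepts.

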##### Economic evaluation outcomes

The cost-effectiveness and cost-utility analysis will be carried out from health system and patient perspectives based on Canadian guidelines [77]. The 2-year costs considered will include all medical services and resources used during hospitalization, emergency department visits, outpatient visits, physician fees and outpatient medications. Patient out-of-pocket costs will include drug co-payments, payments to professionals not covered by the provincial public health insurance coverage, costs related to transportation and time spent by patients while seeking outpatient medical attention, as well as costs related to presenteeism and absenteeism [78]. Program costs associated with the training of facilitators and group meetings will include salaries, benefits, institutional overhead, and opportunity costs [79]. Generalized linear models (GLM) with log link and appropriate distribution (i.e., gamma) will be used to study the difference in costs (Beta estimates) as a function of the intervention (TAU vs SMS) while controlling for potential confounding study factors. Health outcomes will include symptom reduction (BAI) and health-related multi-attribute utility quality of life (AQoL-6D). The number of Anxiety-Free Days (AFD) will be calculated for each BAI scores with a value between 1 (‘anxiety free’) and 0 (‘fully symptomatic’) with linear interpolation to estimate the number of AFDs between baseline and follow up [80]. We will measure quality of life with the AQoL-6D to assess utility estimates [81]. For data analyses, repeated measures will be used to assess the difference (Beta estimates) in health outcomes as a function of the intervention and variables of interest. The incremental cost-effectiveness ratios (ICER) and incremental cost-utility ratios (ICUR) will be calculated based on beta estimates obtained. A discounting rate of 3.5% will be used for future values. We will carry out a sensitivity analysis for estimated values while considering a range of plausible values (95% CI). The ICUR will quantify the trade-off between costs and health-related quality of life.

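### A group effect is stated only for the mixed model; the logistic model for high-end functioning and the cost GLM state no allowance for clustering within SMS groups

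*Protocol article*

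**What the plan says.** Sample size (Protocol article) acknowledges the design feature: "As there is a potential for intraclass correlations (ICC) in an individually randomized group treatment trial". It takes an ICC of 0.02 from a similar study, applies it to the BAI calculation and reports that power would be at least 76%.

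Statistical Analyses, Clinical outcomes, then gives the BAI mixed model random effects for participants nested in SMS groups. That approach is to be repeated on the 12-month and 24-month data. For the high-end functioning question the same section changes model class: "logistic regression models will be used to examine high-end functioning rates". Nothing is said there about the SMS group.

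Economic evaluation outcomes describes the cost model more fully. It is a GLM with log link and gamma distribution, fitted "as a function of the intervention (TAU vs SMS) while controlling for potential confounding study factors". Link, distribution, exposure and adjustment are all mentioned, but a group effect or clustered variance is not.

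Interventions sets the group size at 10 to 15. Trial design offers the SMS program to the control arm after the 12-month follow-up, and the economic section counts costs over 2 years.

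**The concern.** The same patients sit in the same groups whichever outcome is analysed. If shared facilitators and shared sessions can make BAI scores alike within a group, they can do the same for functioning status and service use. Ordinary logistic regression and an ordinary GLM take each patient as an independent observation. With 207 patients randomised to SMS there would be only about 14 to 21 groups (207/15 = 13.8; 207/10 = 20.7). An analyst who follows the text as written would fit one model that allows for this and two that do not.

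With any positive ICC the direction of the error is known: intervals too narrow and p-values too small for the odds ratio and the cost difference. The cost result also feeds further work. The cost-effectiveness and cost-utility ratios are built from the model's beta estimates, and the sensitivity range is set by a 95% CI. If that CI is the model's own, the uncertainty shown to decision makers is too small as well.

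**Working it through.** **Inputs from the article.** BAI difference of 4 points with SD 12.5 ("required to detect a 4-point (pooled SD: 12.5) pre-post treatment difference between SMS + TAU and TAU"); "with an 80% power and α = 0.05", taken as two-sided; 155 analysed per arm; ICC 0.02; groups of 10 to 15; clustering in the SMS arm only.

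**Step 1: reproduce the plan's figures.** The effect size is d = 4/12.5 = 0.32. With the noncentral t distribution, power is 0.7993 at 154 per arm and 0.8019 at 155, so 155 is right. Attrition: 155/(1 − 0.25) = 206.7, so 207 per arm is right.

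For power with clustering, let m be the group size:

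- DE = 1 + (m − 1) × 0.02 in the SMS arm, and 1 in the TAU arm
- SE = 12.5 × √(DE/155 + 1/155)
- power = Φ(4/SE − 1.96)

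This gives 0.770 at m = 10, 0.7605 at m = 12.5 and 0.751 at m = 15. The stated 76% therefore matches the mid-range group size. The plan's own figure is consistent with a design effect confined to the SMS arm.

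**Step 2: cost of ignoring the clustering.** With equal arms and equal variances, true SE / reported SE = √((DE + 1)/2), and the actual two-sided error is 2 × (1 − Φ(1.96/ratio)).

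| ICC | m | DE (SMS arm) | SE ratio | Type I error | 95% CI coverage |
|---|---|---|---|---|---|
| 0.02 | 10 | 1.18 | 1.044 | 0.0605 | 0.9395 |
| 0.02 | 12.5 | 1.23 | 1.056 | 0.0634 | 0.9366 |
| 0.02 | 15 | 1.28 | 1.068 | 0.0664 | 0.9336 |
| 0.05 (assumed) | 10 | 1.45 | 1.107 | 0.0766 | 0.9234 |
| 0.05 (assumed) | 15 | 1.70 | 1.162 | 0.0916 | 0.9084 |

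If 25% attrition fell evenly on the groups, the analysed size would be 7.5 to 11.25. The error would then be 0.0575 to 0.0620 at ICC 0.02, and 0.0691 to 0.0803 at ICC 0.05.

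**Step 3: check on the logistic model itself.** The simulation used beta-binomial SMS groups, independent TAU patients, an assumed 30% event rate, 150 to 160 patients per arm and 60,000 replicates per setting. The rejection rates under no effect were:

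| ICC | 16 groups of 10 | 13 groups of 12 | 10 groups of 15 |
|---|---|---|---|
| about 0 | 0.0480 | 0.0482 | 0.0501 |
| 0.02 | 0.0601 | 0.0616 | 0.0665 |
| 0.05 (assumed) | 0.0748 | 0.0801 | 0.0905 |

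The formula and the simulation agree. The gamma GLM was not simulated, so for costs only the general SE ratio of step 2 applies.

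**The case against.** The strongest defence is that silence is not exclusion. The article gives high-end functioning one clause and the cost model one sentence. Both model families can take a random effect or a clustered variance without changing their name. The article is a condensed text, and a statistical analysis plan that is not shown may supply the detail. This stands to the extent that a reader might infer that the plan has decided to ignore clustering in these models; nothing in the article says so. It does not remove the point. The article states the group structure for one model and omits it for two others, one of which it describes down to link and distribution.

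Three further objections also limit the point:

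- The article speaks of a potential for correlation and gives 0.02 for the BAI alone. A reader might infer that the plan expects correlated functioning or costs, but no ICC is given for either.
- A reader might infer that costs must correlate within groups because members share facilitators and meetings. The article does not support this. A shared program cost creates correlation only if cost per head differs between groups, and all groups receive the same ten sessions with two facilitators. Nor does the article say that program costs are allocated group by group.
- The effect at the plan's own ICC is modest, and the BAI mixed model, including its later repeats, is not touched.

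**Conclusion.** The point holds as a gap between the stated models. The design's clustering is written into the mixed model but not into the logistic or cost models, which as named would give error bars that are too small if outcomes correlate within groups. If the BAI ICC of 0.02 carried over, the true standard error would be about 4% to 7% above the reported one and the two-sided type I error about 6.0% to 6.7%. At an assumed ICC of 0.05 the error would be roughly 7% to 9%.

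These figures assume a two-sided test, equal group sizes, equal arms, no clustering among TAU patients before month 12 and, in the simulation, a 30% event rate. The consequence is limited to secondary question (c) and the cost part of (b); the primary conclusion does not depend on it. It is still worth settling before analysis, because it removes a later choice between clustered and unclustered intervals.

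**What to change.** In Clinical outcomes, state that the logistic model for high-end functioning will include an SMS-group random effect in the SMS arm. Alternatively, state that it will use cluster-robust variance with SMS group as the cluster, each TAU patient as a singleton up to month 12, and a small-sample correction because the groups are few.

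In Economic evaluation outcomes, state that the cost GLM will use the same clustered variance. Treating TAU patients as singletons does not suit the 2-year horizon: those who take up SMS after month 12 may then share groups, so they should carry their delayed-group identifier. The article describes no bootstrap. If one is used for the cost-effectiveness and cost-utility ratios, whole groups should be resampled.

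The cost is a sentence or two in each paragraph. The SMS-arm group identifier is already needed for the primary model; the delayed-group identifier must also be recorded. With 11 per group, intervals widen by about 5% at ICC 0.02 (DE 1.20, √1.10 = 1.05) and by about 12% at an assumed ICC of 0.05 (DE 1.50, √1.25 = 1.12).
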